## Abstract

Migraine is one of the most frequent and expensive neurological disease in the world. Non-pharmacological and digitally administered treatment options have long been used in the treatment of chronic pain and mental illness. Digital solutions increase the patients’ possibilities of receiving evidence-based treatment even when conventional treatment options are limited. The main goal of the study is to assess the efficacy of interdisciplinary digital interventions compared to conventional treatment. The maximum number of participants in this multi-centre, open-label, prospective, randomized study is 600, divided into eight treatment groups. The participants will take part in either a conventional or a digital intervention, performing various tests and interdisciplinary tasks. The primary outcome is expected to be a reduction in the number of headache days. We also undertake to measure various other headache-related burdens as a secondary outcome. The sample size, digital interventions not conducted via video calls, the lack of human connection, limited intervention program, and the conducting of studies only in digitally sophisticated countries are all significant limitations. However, we believe that digitally mediated treatment options are at least as effective as traditional treatment options while also allowing for a significantly higher patient throughput. The future of chronic disease treatment is remote monitoring and high-quality digitally mediated interventions.The study is approved by the Ethics Committee of the University of Tartu for Human Research (Permission No. 315T-17, 10.08.2020) and is registered at ClinicalTrials.gov: NTC05458817 (14.07.2022).

## 1. Background

The prevalence of migraine in the adult population of the world is around 12% [1] in Europe 14.7% [2] and in Estonia 17.7% [3]. Migraine is an expensive disease, costing the European economy 95 billion euros annually and migraine sufferers miss between 2 and 46 days of work annually (absenteeism). Presenteeism, which reduces workability, productivity, and efficiency, is high in migraine sufferers and, thereby harms the economy [1,4,5].

In addition to pharmacological treatments, non-pharmacological interventions (NI) are important in migraine management, encompassing patient participation, self-help skills, and various approaches such as patient education, headache nurse counselling, cognitive behavioural therapy and physiotherapy [6–11]. Headache nurses, through education and counselling, have demonstrated positive effects on the functioning of migraine patients, highlighted also in Kristi Tamela’s MSc thesis in Estonia [8–10]

While relaxation techniques, progressive muscle relaxation, biofeedback, and cognitive behavioral therapy (CBT) were formerly considered Level A therapies with an excellent safety profile, the 2019 Cochrane systematic review revealed insufficient high-quality data to determine the effectiveness of psychological therapies for migraine prevention and treatment in adults [6,7,11].

The efficacy of physiotherapy, another NI component, varies depending on the headache diagnosis, with contradictory results regarding its effectiveness in migraine treatment. Physiotherapeutic treatment aims to address peripheral and central hypersensitivity, alleviate neck-shoulder strain, and reduce pain and vestibular symptoms [12,13]. Although NI are a promising addition to medication, these interventions require more resources and are not universally accessible to migraine patients.

In the contemporary digital era, technology-based treatments play a pivotal role in monitoring health, organizing interventions, facilitating communication among healthcare providers, and supporting individuals with chronic diseases and mental health issues [14–16]. Digital solutions offer substantial potential to enhance access to education, counselling, and NI, particularly benefiting patients constrained by time, finances, or transportation access [17–27].

Despite existing digital applications for migraine treatment, there is a need for improvement. Predominantly researches are focusing on the applicability of digital diaries and limited is exploration of comprehensive interdisciplinary digital NI and their effectiveness [28].

One of the most popular mobile applications Migraine Buddy records headache days, tracks headache triggers, patterns, coping tactics and more [29]. Similar digital headache diaries (DHD) and assistants can monitor migraines and train health-related habits with minimal data loss, over 80% compliance, user-friendly solutions, patient acceptance, and a low perceived burden on daily life [30].

Digital CBT and digitally administered relaxation techniques has been shown to be successful in the treatment of mood and anxiety disorders, insomnia, and can be used to ease other accompanying emotional difficulties in people with migraine [31–36]. Digital physiotherapy, cost effective and accessible through online programs, aligns with current treatment guidelines for various chronic diseases, promoting physical activity and interdisciplinary treatment concepts [37,38].

Limited studies have investigated the effectiveness of patient’s interactions with headache nurses, virtual nurses or virtual agents. For example, the Help4Mood platform uses a virtual avatar for depression treatment [39]. Virtual nurses play a role in collecting medical data, providing assistance, motivating patients, and enhancing treatment adherence [40].

Several authors have concluded that with NI, the creation of an effective, novel, and evidence-based digital therapeutic (DTx) platform would improve patient self-management [40] Notably, there is currently a lack of published articles on comprehensive digital intervention programs specifically designed for migraine.

Studies on technology-based interventions (TBI) and apps for chronic disease primarily emphasize applicability, functionality, user experience, and desirable attributes, with less understanding of their effectiveness in achieving long-term behavioral change [17–27].

Key issues with digital solutions include the absence of real-time therapist/patient interaction, challenges in delivering personalized and timely feedback, difficulties in TBI delivery, regional variability in digital solution availability, issues in generating patient intervention reports or summaries, data protection concerns and potential data loss due to technical, internet connection, programme compatibility, software or hardware issues [12,27,40].

Managing headaches involves a multifaceted approach, encompassing pharmacological and NI treatments, preventative methods, lifestyle changes, and self-monitoring [41,42]. Previous research indicates that users often discontinue digital CBT early, facing challenges in maintaining adherence without sufficient clinical contact [43,44]. Studies on internet-based CBT for depression highlight the impact of depression severity on dropout rates, necessitating continuous monitoring [45]. Future research should explore the influence of anxiety and depression on the treatment adherence of a headache patient. Furthermore, it is unknown whether evidence-based digital therapies can successfully be used outside of clinical practice (i.e., self-help with minimal or no clinical intervention) [41,44].

The effectiveness of DHDs compared to conventional ‘paper-pencil’ headache diaries (PD) remains uncertain, and their impact on treatment adherence is unclear. In conventional diaries, patient often pre-fill fields or mark the conditions later [46–48]. Previous studies indicate that factors such as age, gender, season, day of the week, headache frequency, headache severity, headache medication use, and DHD completion time may all influence a adherence to diary filling [47]. Identifying the elements, background factors and reminders influencing DHD completion is crucial for this study.

Future studies on digital interventions should focus on quantifying the impact of digitally mediated behavioral interventions on pain intensity and psychiatric symptoms. No research has determined the ‘optimal dose’ of behavioral interventions, including the required number and duration of CBT sessions [44]. The effectiveness and successful digital application of evidence-based CBT with minimal clinical involvement also require investigation.

Limited studies have explored virtually mediated nurse counselling and digital physiotherapy. While a virtual nurse (avatar) may address healthcare challenges, it cannot diagnose or collaborate with other team members [40]. Online chatroom counselling with nurses offers opportunities to enhance clinical contact in digitally mediated interventions, but various limitations and challenges need addressing [49]. To our knowledge, the efficacy of digital physiotherapy in interdisciplinary headache treatments remains unstudied. A global shortage of headache specialists, including clinical psychologists, CBT therapists, physiotherapists, and headache nurses, contributes to long waiting lists and limited availability. Geographic constraints further impede access to services, particularly for those residing far from large centers. Digital NI options address these challenges by expanding access to services, utilizing professional intervention methods, reducing dropout rates, and thereby improving intervention efficacy [50,51].

The main goal of the present study is to assess the efficacy of interdisciplinary digital interventions compared to conventional treatment options.

The essential secondary objectives encompass evaluating individual and combined components of interventions, including adherence, credibility, clinical contact, and cost-effectiveness in comparison to conventional format.

## 2. Methods and design

### 2.1 Ethics statement

The procedures for and design of the study were approved by the Ethics Committee of the University of Tartu for Human Research (Permission No. 315T-17) and the study is registered at ClinicalTrials.gov: NCT05458817.

### 2.2 Study design

This is a multi-centre, open-label, prospective, randomized, and controlled study on the interdisciplinary intervention of migraine with digital technology-mediated treatment options versus conventional treatment options.

In the preparation phase of the study, migraine patients and specialists from Estonia contributed to the project. They assessed the Migraine Buddy application [29] and found it to be overly difficult, especially during the aura and attack phases of a migraine. The data of the application must also be available to specialists and compatible with e-health.

While preparing and planning the study, it became clear that no interdisciplinary digital solution for the treatment of headaches currently exists. Existing solutions are mostly digital headache diaries with individual appendices. There is no solution that brings comprehensive treatment, including nurse counselling, psychotherapy, and physiotherapy, to the patient.

In 2020, Migrevention started developing an interdisciplinary mobile application and specialist dashboard for migraine patients. They conducted validation interviews with Estonian migraine patients before developing the digital solution. Validation interviews showed that patients are ready to implement digital education, CBT, and physiotherapy programs into their treatment plan. The development of the Migrevention application provided a good opportunity to study a digitally mediated interdisciplinary headache treatment and compare it with conventional treatment options. For this reason, we use the Migrevention application, which monitors the patient’s use of the system, andobtains information about patient preferences, their health behavior, the actual application of patients’ self-help skills, their need for clinical intervention, etc. The digital format allows for reminders and follow-ups on patients, enabling researchers or clinicians to monitor data in real-time. The importance of this has also been emphasized in previous studies [52]

### 2.3 Planned sample size

In order to devise the sample size, we conducted an estimated power analysis to establish the size of the groups (75 patients in each group) and strive for 80% power. Hence, the maximum estimated number of participants is 600.

The sample comprises consecutive migraine patients who meet the inclusion criteria and visit a neurologist in a partner clinic. In section 2.5, the precise involvement of patients is outlined.

Consent to participate in the research is voluntary and does not affect the patient’s ability to use the Migrevention solution or their usual minimal treatment options.

### 2.4 Participants inclusion and exclusion criteria

Inclusion criteria:

Diagnosis of frequent episodic migraine, headache days per month 4–14 daysAge 18–64 yearsVery good command of the Estonian language, both orally and in writing

Exclusion criteria:

All other diagnoses of primary and/or secondary headachesCurrently existing severe depressionHistory of psychotic disorder(s)Pregnancy or lactationSevere somatic disorder(s)History of severe organic psychiatric disorder(s)History of other chronic pain condition(s)History of addictive disorder(s)

### 2.5 Primary outcome measure

The primary outcome measure is a reduction in the number of headache days (data derived from diaries) three months after the end of the interdisciplinary intervention programmes compared to the baseline (at the start of intervention).

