### 2.6 Secondary outcome measures

The secondary outcome measures are as follows: number of headache days six and nine months after finishing intervention (follow-up) (data derived from diaries); change in consumption of analgesics or triptans (data derived from diaries); change in pain intensity (data derived from diaries); changes in depression, anxiety scores (data derived from tests); increase in pain acceptance (data derived from tests); changes in quality of life (data derived from tests); changes in number of sick-leave days (data derived from the national e-health system); and assessment of impact on the burden of migraine through sick-leave days, disability rate, and specialist visits (data derived from e-health systems). Specific methods are presented in Table 1 and Table 2.

**Table 1 pdig.0000295.t001:** Methods used in the study.

Indicator	Method	Time	Procedures for use	Patient time for filling test	Investigator
Frequency of headaches	Digital diary, paper diary	Continuous	Continuous	> 2 minutes	Patient independently in the application or on paper
Medication use	Digital diary, paper diary	Continuous	Continuous	> 2 minutes	Patient independently in the application or on paper
Medication use	Prescription Centre	Continuously/Intervals ^1^	Continuously/Intervals ^1^	N/A	Specialist desktop/doctor or nurse.
The effect of headaches on everyday life	Headache Impact Test (HIT-6) [53]	Intervals ^1^	Intervals ^1^	2–5 minutes	The patient performs independently in the application or the test environment REDCap.
Screening for mental disorders	Emotional State Questionnaire (ESQ-2) [54]	Intervals ^1^	Intervals ^1^	2–5 minutes	The patient performs independently in the application or the test environment REDCap.
Mental disorders	Diagnostic and Statistical Manual of Mental Disorders, Fifth Edition (DSM-V) symptom checklist + Psychiatrist consultation (if DSM-V symptom checklist detects a mental health disorder	Intervals ^3^	Intervals ^3^	60 minutes	The patient performs independently in the application or the test environment REDCap and/or one psychiatrist appointment
Personality profile	Swedish Universities Scales of Personality (SSP) [55]	Once at the beginning of the study	Once at the beginning of the study	30 minutes	The patient performs independently in the the test environment REDCap.

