### 2.9 Data collection

Data collection occurs digitally on the mobile application, in the online research environment of the National Centre for Transitional Medicine and Clinical Research—REDCap, and at specialist receptions in parallel. The volume of data collected varies from group to group and depends on the randomization. Participants in the digital group complete the tests on the mobile application and in the REDCap environment. Participants in the control group fill in the tests and the satisfaction questionnaire in the REDCap environment. Specialists fill in the satisfaction questionnaire in the REDCap environment.

In addition to the data from tests and databases, the following data will be collected:

1) frequency of headache days; 2) pain intensity; 3) medications used; 4) performance of tasks sent or set by the headache nurse; 5) performance of the tasks sent or set by a CBT therapist; 6) performance of the tasks sent or set by a physiotherapist.

During the research, several parameters will be measured. The longest time will be devoted to the patient’s completion of the tests at the beginning and end of the study—2–2.5h. The time required to complete the tests each week is between 5and 10 minutes. The methods used in the study are presented in more detail in Table 2. The testing data collected in all groups are presented in Table 3.

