### 2.10 Interventions

NI conducted with the participants are detailed in Table 4. All materials sent to participants through the Migrevention Clinical solution (study group) or explained in a face-to-face appointment (control group) are based on the intervention manual and are the same in both groups. The discussion topics and materials are distributed in the order specified in the intervention manual. Since the study attempts to mimic a standard conventional intervention as closely as possible, in the case of conventional treatment (control group), the communication between the specialists and participants is not precisely described in the intervention manual, leaving each specialist free rein over communication.

**Table 4 pdig.0000295.t004:** Interventions by group.

	Study group (digitally mediated NI)	Control group (conventionally mediated NI)
Headache diary	Participant is filling DHD in the Migrevention Clinical mobile application.	Participant is filling PHD, usually used in conventional treatment.
Headache nurse counselling	The headache nurse sends self-help materials (previously recorded audio) to the participant through the Migrevention Clinical specialist dashboard and communicates with the patient through the chatroom connected to the Migrevention Clinical mobile application. The Participant receives notifications to the Migrevention Clinical mobile application about new tasks, listens to the materials, and if needed, asks the headache nurse additional questions via the chatroom. Communication through the chatroom is not limited.	The headache nurse arranges face-to-face meetings with the participant to provide conventional nurse counselling. Meetings take place only at agreed times.

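### Headache days are recorded in the app in every digital group and on paper in every control group, so recording differences cannot be separated from the treatment effect

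*Protocol article*

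**What the plan says.** Section 2.5 of the protocol article sets the primary outcome as "a reduction in the number of headache days (data derived from diaries", taken three months after the programme ends and "compared to the baseline (at the start of intervention". Table 1 (section 2.6) lists a digital and a paper diary as the methods for headache frequency, completed by the "Patient independently in the application or on paper".

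Table 3 (section 2.8) assigns the digital diary to study groups I to IV and the paper diary to control groups I to IV. Table 4 (section 2.10) confirms this. In the study groups, "Participant is filling DHD in the Migrevention Clinical mobile application"; in the control groups, "Participant is filling PHD, usually used in conventional treatment".

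On the two formats, the Background states: "In conventional diaries, patient often pre-fill fields or mark the conditions later". It adds that how the digital diary compares with paper is uncertain and that the effect on adherence is unclear. It also credits app diaries with little data loss. Section 2.2 says of the digital side: "The digital format allows for reminders and follow-ups on patients, enabling researchers or clinicians to monitor data in real-time".

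The limitations in section 3 do not mention that the primary outcome is measured with a different instrument in each type of arm.

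**The concern.** The diary does two jobs. It is a component of the randomised treatment, and it is the instrument that measures the primary outcome. Because its format follows the arm without exception, a difference in recording looks exactly like a difference in headache days.

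The error could go either way. If paper users miss headache days, control counts fall and digital treatment looks worse than it is. If app users stop entering headache days, digital counts fall and digital treatment looks better. The second case matters because section 3 says the authors intend to show that digital treatment is no less effective than conventional treatment. A larger sample does not help: it narrows the interval around a biased estimate.

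**Working it through.** **1. Is the confounding complete?** In Table 3, 4 of 4 digital groups have the app diary and 4 of 4 control groups have paper. An indicator for app diary equals the indicator for digital arm in 8 of 8 groups. No model for a paired or pooled digital-versus-conventional contrast can estimate the two separately. In pair I (study group I v control group I) nothing but the diary differs.

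**2. The plan's own figure.** 8 × 75 = 600 reproduces. The 75 per group cannot be reproduced, because the article does not give the inputs. Back-solving with assumed two-sided 5% and 80% power: (1.960 + 0.842) × √(2/75) = 0.457 SD. This serves only as a yardstick.

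**3. How large could the recording bias be?** From the document: the entry range of 4–14 headache days a month (section 2.4). Assumed: 8 true days a month, SD of the change score 4 days, 10% differential recording.

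- Bias at follow-up only, none at baseline, true count still 8: 10% × 8 = 0.8 day; 0.8/4 = 0.2 SD. At the entry limits the spurious difference is 10% × 4 = 0.4 day and 10% × 14 = 1.4 days.
- The same with 5% differential recording: 5% × 8 = 0.4 day; 0.4/4 = 0.1 SD.
- The same 10% at both times, with baseline taken from the same diary and an assumed true reduction of 2 days: recorded change is 0.9 × 2 = 1.8 days, a spurious difference of 0.2 day; 0.2/4 = 0.05 SD.

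Which case is closer depends on how baseline is collected and whether capture changes over time. Section 2.5 places baseline at the start of the intervention but does not name the instrument.

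**4. Effect on false positives.** With no true treatment difference, net bias b in SD units and a two-sided 5% test (normal approximation):

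rejection rate = 1 − Φ(1.96 − b/√(2/n)) + Φ(−1.96 − b/√(2/n))

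For n = 75, √(2/75) = 0.1633. For n = 300 (four groups pooled), √(2/300) = 0.0816.

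| Net bias b (SD) | 75 v 75 | 300 v 300 |
|---|---|---|
| 0.05 | 6.1% | 9.4% |
| 0.1 | 9.4% | 23.2% |
| 0.2 | 23.2% | 68.8% |

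**5. Can another contrast remove it?** Pair II, III or IV minus pair I would cancel a constant additive format effect. Its standard error is √(4/75) = 0.231 SD, so it detects 2.802 × 0.231 = 0.647 SD at 80% power and has 50.8% power at 0.457 SD. It estimates the digital-versus-conventional difference for the added components only, not for the whole package.

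**The case against.** The strongest reply is that the diary is meant to be part of the package. The trial compares digital care as delivered with conventional care as delivered, and section 2.10 says it tries to resemble usual care. This stands as a reason to keep both diaries as interventions. It does not justify using them as the only measure of the primary outcome, because a real effect of the diary still cannot be told from a difference in recording.

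The second reply is that change from baseline removes the problem. It does so in part: an additive bias that is constant over time cancels if baseline uses the same diary, and a constant proportional one shrinks to about 0.05 SD under the assumptions above.

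A reader might also infer more than the document supports:

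- That 23% and 69% are the expected error rates. They need the full 10% bias at follow-up and none at baseline.
- That diary completion is known to decline at different rates in app and on paper. The Background calls the effect on adherence unclear, and its remark on paper diaries concerns when entries are made, not how many are lost.
- That medication use has no source but the diary. Table 1 also lists the Prescription Centre, although section 2.6 defines the change in analgesics or triptans from diaries.
- That the questionnaires share the problem. Section 2.9 says "Participants in the digital group complete the tests on the mobile application and in the REDCap environment", while controls use REDCap only. Both are self-completed electronically, and the document gives no reason to expect a bias like that between app and paper.

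**Conclusion.** The point holds as a design weakness. Diary format and arm type coincide in all eight groups, so the planned digital-versus-conventional contrast on diary-derived headache days cannot separate recording from treatment, paired or pooled. An analysis plan cannot repair this with the diaries alone, and a common measurement cannot be recovered after data collection.

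Neither the size nor the direction of the bias can be determined from the document. Under assumed values (SD of change 4 days, 8 days a month, up to 10% differential recording), a plausible range is 0.05 to 0.2 SD. That corresponds to false-positive rates of about 6% to 23% for one pair and 9% to 69% for the pooled comparison. The lower end applies if the bias is constant and baseline comes from the same diary. The upper end applies if it is present only at follow-up.

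**What to change.** Collect one short headache-day item in REDCap, worded identically and with the same recall period, in all eight groups. Ask it once at consent before randomisation, and again 3, 6 and 9 months after the intervention. Because the baseline item uses recall, no run-in is needed and the consent-to-randomisation sequence in section 2.7 is unchanged.

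Pre-specify the digital-versus-conventional comparison on this item as a key supporting analysis, or as the primary analysis if the sponsor accepts recall. Base any conclusion that digital treatment is no less effective on agreement between this result and the diary result. Report diary completeness by arm, with a sensitivity analysis for differential recording. State which instrument supplies the diary baseline.

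The cost is small: section 2.9 already has all groups using REDCap and plans 5 to 10 minutes of tests each week. The downsides are slight extra burden, recall error, and the chance that patients copy the answer from their app or paper diary. Reporting bias from the open-label design remains.
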